## Abstract

**Introduction:**

Short-term metabolic and observational studies suggest that protein intake above the recommended dietary allowance of 0.83 g/kg body weight (BW)/day may support preservation of lean body mass and physical function in old age, but evidence from randomised controlled trials is inconclusive.

**Methods and analysis:**

The PRevention Of Malnutrition In Senior Subjects in the EU (PROMISS) trial examines the effect of personalised dietary advice aiming at increasing protein intake with or without advice regarding timing of protein intake to close proximity of usual physical activity, on change in physical functioning after 6 months among community-dwelling older adults (≥65 years) with a habitual protein intake of <1.0 g/kg adjusted (a)BW/day. Participants (n=264) will be recruited in Finland and the Netherlands, and will be randomised into three groups; two intervention groups and one control group. Intervention group 1 (n=88) receives personalised dietary advice and protein-enriched food products in order to increase their protein intake to at least 1.2 g/kg aBW/day. Intervention group 2 (n=88) receives the same advice as described for intervention group 1, and in addition advice to consume 7.5–10 g protein through protein-(en)rich(ed) foods within half an hour after performing usual physical activity. The control group (n=88) receives no intervention. All participants will be invited to attend lectures not related to health. The primary outcome is a 6-month change in physical functioning measured by change in walk time using a 400 m walk test. Secondary outcomes are: 6-month change in the Short Physical Performance Battery score, muscle strength, body composition, self-reported mobility limitations, quality of life, incidence of frailty, incidence of sarcopenia risk and incidence of malnutrition. We also investigate cost-effectiveness by change in healthcare costs.

**Discussion:**

The PROMISS trial will provide evidence whether increasing protein intake, and additionally optimising the timing of protein intake, has a positive effect on the course of physical functioning after 6 months among community-dwelling older adults with a habitual protein intake of <1.0 g/kg aBW/day.

**Ethics and dissemination:**

The study has been approved by the Ethics Committee of the Helsinki University Central Hospital, Finland (ID of the approval: HUS/1530/2018) and The Medical Ethical Committee of the Amsterdam UMC, location VUmc, Amsterdam, the Netherlands (ID of the approval: 2018.399). All participants provided written informed consent prior to being enrolled onto the study. Results will be submitted for publication in peer-reviewed journals and will be made available to stakeholders (ie, older adults, healthcare professionals and industry).

**Trial registration number:**

ClinicalTrials.gov Registry (NCT03712306).

Strengths and limitations of this studyThis large randomised controlled trial addresses a key question whether dietary advice to increase protein intake to ≥1.2 g/kg adjusted body weight (aBW)/day is beneficial for physical functioning in community-dwelling older adults.This trial will also examine the additional effect of the timing of protein intake in close proximity of usual physical activity on change in physical functioning.Participants included had a habitual protein intake of <1.0 g/kg aBW/day.The lack of blinding of the study participants and nutritionists who also collect data on all outcome measures is a limitation of the study design.Another limitation of this study is that the biological value of the total protein intake (ie, type of amino acids) is unknown.

## Introduction

There is an ongoing debate on whether or not older adults should be recommended a protein intake above the current recommended daily allowance (RDA) established by the European Food Safety Authority (EFSA) of 0.83 g/kg body weight (BW)/day for adults.^1^ International panels of geriatricians, nutritional experts and scientists have proposed at least 1.0–1.2 g protein/kg BW/day for healthy older adults in order to maintain and regain muscle mass, strength and function.^2 3^

The proposed increase of the RDA for older adults is merely based on results from short-term metabolic and epidemiological studies. Several metabolic studies showed that older adults (≥65 years) have a lower muscle protein synthesis (MPS) following protein intake compared with younger adults,^4–6^ and that higher protein intake enhances MPS in older adults when compared with lower protein intake (1.2 g/kg BW/day vs 0.8 g/kg BW/day,^7^ or ≥30 g/day vs 15 g/day^8^). In addition, the anabolic threshold (ie, optimal dose of dietary protein in a meal that stimulates MPS) is 70% higher in older compared with younger adults.^5^ Epidemiological studies have shown that higher dietary protein intake in older adults, defined as >0.9 g/kg BW/day^9^ or >1.0 g/kg BW/day^10–12^ is associated with lower risk of weight loss,^11^ better disability trajectories,^12^ less loss of lean mass^9^ or lower risk of developing functional impairments.^10^

Despite the evidence from metabolic and epidemiological studies, causal evidence to support beneficial effects of protein intake at or above 1.0 g/kg BW/day based on randomised controlled trials (RCTs) is not conclusive. One systematic review showed no beneficial effect of increasing protein intake on lean body mass, muscle cross-sectional area, muscle strength or physical performance.^13^ Of the 36 studies included in the systematic review, 26 studies presented mean habitual protein intake of the study participants which ranged between 0.78 and 1.5 g/kg BW/day, with only one study below the protein RDA of 0.8 g/kg BW/day.^13^ The relatively high mean habitual protein intake may explain the absence of a beneficial effect of additional protein. Another explanation may be that the amount of protein provided might not have been sufficient to augment MPS. That is, a protein intake of 25–30 g is required to stimulate MPS and maintain muscle mass,^14 15^ though the amounts provided varied between 10 g/day (3 days/week) and total intake of 125 g/day or were not reported. Of the trials published after the systematic review, Park *et al* showed that intake of 1.5 g/kg BW/day for 12 weeks resulted in higher muscle mass and improved gait speed compared with intake of 0.8 g/kg BW/day in undernourished prefrail and frail older adults.^16^ Ten Haaf *et al* showed a positive effect of increasing protein intake for 12 weeks on lean body mass in active older adults with a habitual protein intake of <1.0 g/kg BW/day.^17^ Beelen *et al* found no effects of protein supplementation on physical performance among older adults after hospital discharge,^18^ however, baseline protein intake was already 1.0 g/kg BW/day in the control group and 1.5 g/kg BW/day in the intervention group. Finally, Bhasin *et al* showed no beneficial effects other than a decrease in fat mass after a controlled diet with 1.3 g/kg BW/day of protein for 6 months compared with a control diet consisting of 0.8 g protein/kg BW/day^19^ among functionally limited community-dwelling men aged ≥65 years. However, mean body mass index (BMI) of the participants was quite high (30.3 kg/m^2^), which may have resulted in an overestimation of baseline protein requirements. Based on inconsistent findings, more RCTs in older adults with lower habitual protein intake are needed to determine the potential effect of increasing protein intake on physical functioning outcomes.

Previous studies among older adults showed that protein supplementation in combination with resistance exercise has more beneficial effects on body composition, muscle strength and physical function compared with resistance exercise alone.^20–26^ The underlying hypothesis is that protein supplementation augments the adaptive response of skeletal muscle to resistance exercise. In addition, there is evidence that timing of protein intake in close proximity of physical activity stimulated MPS to greater extent than when timed at other hours during the day.^27^ To our knowledge, there are no RCTs investigating the effect of timing protein intake in close proximity of physical activities on physical functioning.

The PRevention Of Malnutrition In Senior Subjects in the EU (PROMISS) trial is designed to fill in some of the current knowledge gaps on the optimal amount of dietary protein in older community-dwelling adults and timing of protein intake in relation to physical activity. Its primary objective is to examine the effectiveness of personalised dietary advice aiming at increasing protein intake to at least 1.2 g/kg adjusted (a)BW/day on change in physical functioning after 6 months measured by change in walk time using a 400 m walk test among community-dwelling older adults with a habitual protein intake of <1.0 g/kg aBW/day. Additionally, it examines the combined effect of personalised dietary advice aiming at increasing protein intake to at least 1.2 g/kg aBW/day and advice aiming at optimising the timing of protein intake in close proximity of usual physical activity. The secondary objectives are to examine the effectiveness of personalised dietary advice aiming at increasing protein intake to at least 1.2 g/kg adjusted on 6-month changes in physical functioning measured by the Short Physical Performance Battery (SPPB) score, muscle strength, body composition, self-reported mobility limitations, quality of life (QoL), incidence of frailty, incidence of sarcopenia risk, and incidence of malnutrition and change in healthcare costs.

In three ancillary studies the following additional objectives are addressed; (1) the effect of using persuasive technology on adherence to personalised dietary advice aiming at increasing protein to at least 1.2 g/kg aBW/day, (2) the effect of personalised dietary advice aiming at increasing protein intake to at least 1.2 g/kg aBW/day on the oral and gut microbiota composition, and (3) the effect of personalised dietary advice aiming at increasing protein intake to at least 1.2 g/kg aBW/day on central neural responses to food-cues in brain areas of interest.

## Methods and analysis

### Study design

The PROMISS trial is a multicentre RCT designed to examine the effectiveness of personalised dietary advice aiming at increasing protein intake and advice on optimising the timing of protein intake in close proximity of usual physical activity on change in physical functioning after 6 months. Participants will be randomised into three groups: one control group (no intervention); intervention group 1 receiving personalised dietary advice aiming at increasing protein intake to at least 1.2 g/kg aBW/day; and intervention group 2 receiving personalised dietary advice aiming at increasing protein intake to at least 1.2 g/kg aBW/day, including personalised advice to optimise the timing of protein intake in close proximity of usual physical activity.

### Eligibility criteria

The eligibility criteria are proposed to include a study group of community-dwelling older adults (65+ years) with a habitual protein intake <1.0 g/kg aBW/day. Inclusion and exclusion criteria are listed in box 1, and some are described in more detail below.

Box 1Eligibility criteria for participation of the PROMISS trialInclusion criteriaCommunity dwelling.Age ≥65 years.Habitual protein intake <1.0 g protein/kg aBW/day.BMI ≥18.5 kg/m^2^ and ≤32.0 kg/m^2^ (based on measured weight and height).Ability to walk 400 m within 15 min, without the use of a walker and no rest longer than 60 s.Exclusion criteriaInability or unwillingness to provide informed consent.Not able to eat independently (self-reported).Not able to speak, write and read the local language (Finnish or Dutch).Current participation in supervised behavioural or lifestyle intervention that intervenes with the PROMISS trial.Not able to visit the research site in the next 6 months.Bedridden, wheelchair users or always being inside.Diagnosis of severe kidney disease (self-reported).Parkinson’s disease (self-reported).Diagnosis of type I diabetes mellitus (self-reported).Diagnosis of type II diabetes mellitus and requiring use of insulin started within 6 months (self-reported).Current treatment of cancer (with the exception of basal cell carcinoma).Vegan diet.Severe allergies to certain food product (peanut, gluten).Diagnosis of an eating disorder (self-reported).Purposefully lost/gained >3 kg in the past 3 months.Heart problems in the past 3 months, defined as heart attack, angioplasty, heart surgery, stroke, severe shortness of breath during physical activity (self-reported).Alcohol abuse during past 6 months, defined as the AUDIT-C score ≥3.^90^Low cognitive status, defined as the MMSE score ≤20.^35^aBW, adjusted body weight; AUDIT-C, Alcohol Use Disorders Identification Test-Concise; BMI, body mass index; MMSE, Mini-Mental State Examination; PROMISS, PRevention Of Malnutrition In Senior Subjects in the EU.

Older adults with a BMI of <18.5 kg/m^2^ will be excluded, because these participants are likely to be undernourished^28^ and should preferably receive general nutritional care that is not provided in this trial. Those with a BMI of >32.0 kg/m^2^ will be also excluded, because a high BMI (>30.0 kg/m^2^) is associated with poorer physical function^29^ and disability^30^ in old age, and intentional weight loss by lifestyle interventions leads to a reduced mortality risk.^31^ In light of this evidence, older adults with a BMI >32.0 kg/m^2^ should preferably be advised to lose weight, which is not the aim of the present study and may interfere with the study objective. Because participants of intervention group 2 will be advised to consume protein-rich foods in close proximity of usual physical activity, older adults who are bedridden, wheelchair users or do not go outside will be excluded from the trial. Older adults with a diagnosis of severe kidney disease (ie, treatment of a nephrologist and/or protein-restricted diet, self-reported) will also be excluded as they should be advised to limit their protein intake.^2 32–34^ Older adults with a low cognitive status (Mini-Mental State Examination (MMSE) score ≤20^35^) will be excluded, as participants should be able to understand and follow dietary advice if randomised to one of the intervention groups.

#### Calculation of protein intake using aBW

To calculate habitual protein intake in g/kg aBW/day for all (potential) participants and recommended protein intake (participants in the two intervention groups), we apply aBW depending on participants’ age and BMI. We use aBW because underweight persons require extra protein to build muscle tissue, while in overweight persons, much ‘extra weight’ is adipose tissue. Protein intake in g/kg aBW/day is based on self-reported BW during screening and afterwards based on measured BW during the baseline assessment, which is further used throughout the study. For those with a BMI >25.0–32.0 kg/m^2^ (age ≤70 years) or >27.0–32.0 kg/m^2^ (age >70 years), we apply aBW corresponding to a BMI of, respectively, 25.0 or 27.0 kg/m^2^. For those with a BMI >18.5–<22.0 kg/m^2^ (age >70 years), we apply aBW corresponding to a BMI of, respectively, 18.5 or 22.0 kg/m^2^.^36^ For the recommended protein intake, we apply aBW which is based on baseline measured BW.

### Recruitment and screening

Two hundred and sixty-four community-dwelling adults aged 65 years and older will be recruited at two study sites (metropolitan area of Finland including Helsinki, Espoo, Vantaa, Kauniainen, and Amsterdam, the Netherlands). The recruitment strategy includes mass mailing using addresses obtained from a random sample of the Finnish Population Registry (in Finland only), newspaper advertisements, media coverage, lectures, oral presentations to the target group, informing professionals working with older adults and flyers which will be distributed at locations where many community-dwelling older adults visit.

Older adults who are interested in participating will be asked to contact the local PROMISS research team (by phone or by email). Thereafter, screening by phone takes place, only when verbal informed consent is given, in which the majority of the eligibility criteria will be assessed along with an explanation of the study. Only those with a lower habitual protein intake (<1.0 g/kg aBW/day) will be invited for the first clinic visit. Assessment of habitual protein intake will be estimated in two steps: (1) initial screening by phone; (2) a full dietary assessment based on a combination of three food diaries and three 24-hour dietary recalls to confirm lower habitual protein intake. Step 1, the initial screening is performed by phone using the Protein Screener 55+ (Pro55+, available for use in English, Finnish and Dutch: see www.proteinscreener.nl/%23/). This screening tool was specifically developed and validated for this purpose.^37^ The screening results in a probability score (0%–100%) of having a protein intake below 1.0 g/kg aBW/day. At a probability of >30%, sensitivity and specificity are optimally balanced.^37^ In the PROMISS trial we select persons with a probability score varying between >15% (when initial response rates to recruitment strategies are low) and >30% (when initial response rates are high), for the second step of assessing habitual protein intake. Those who fulfil the eligibility criteria receive further information on the study and a food diary with a booklet with pictures of portion sizes by post to support the 24-hour dietary recalls. After a minimum of 1 week of consideration, the research staff contacts the older adults, and among those who are still willing to participate the full dietary assessment will take place (step 2). These potential participants will be asked to keep track of their dietary intake by filling out the provided food diary for 3 consecutive days (3 weekdays; or 2 weekdays and 1 weekend day). The booklet with pictures of portion sizes that they received earlier will help them accurately fill out the diary. Each day after, they will be called by a nutritionist to go through their food diary of the day before (24-hour dietary recall). Potential participants are asked whether these days are representative for their habitual diet. In case one of the 3 days is not representative, mean protein intake is based on 2 instead of 3 days. In case of more than 1 non-representative day, the person will be excluded. The food intake data based on the 24-hour dietary recall will be entered into the program ‘Fineli’ for the Finnish data^38^ and into the program ‘Eetmeter’ of the Dutch Nutrition Center using an extended version of the Dutch Food Composition Table of 2016 for the Dutch data^39^ to calculate intake of macronutrients and micronutrients (vitamin D and vitamin B_12_). Participants with an actual protein intake ≥1.0 g/kg aBW/day (based on self-reported BW) will be excluded.

Potential participants with a mean habitual protein intake <1.0 g/kg aBW/day (based on the three 24-hour dietary recalls) will be invited for the clinic visit, where final eligibility criteria will be assessed; MMSE >20, ability to walk 400 m within 15 min (the use of a cane is allowed, but without the use of a walker and no rest longer than 60 s), and BMI of ≥18.5 kg/m^2^ and ≤32.0 kg/m^2^ based on measured BW and body height. When all eligibility criteria are met, participants are included in the PROMISS trial.

### Randomisation, allocation and masking

Randomisation by means of a stratified block randomisation procedure will be performed by an independent statistician. Participants will be allocated in a 1:1:1 ratio to the three groups. The size of the randomisation blocks is three. Participants will be stratified according to their baseline habitual protein intake (<0.9 or 0.9–1.0 g/kg aBW/day) and sex to ensure homogeneous distribution of baseline habitual protein intake and sex in the three groups across the two recruitment sites, because there may be a different intervention effect by baseline habitual protein or sex. In case couples are eligible, we will allocate them to the same intervention group to limit interference between intervention groups. We will randomly select on which partner the randomisation for the intervention group is based. Any resulting unbalance in the number of subjects per treatment arm will be corrected in the randomisation of the next block. Due to the nature of the study, researchers, nutritionists and participants are not blinded to the study group.

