### Study timeline

The first clinic visit starts with written informed consent, and when participants are eligible, the baseline assessment will be performed. The baseline assessment consists of questionnaires (frailty status, risk of sarcopenia, self-reported mobility limitations, QoL and healthcare costs) and measurements (physical function, muscle strength and body composition). See below ‘primary and secondary outcomes’ and ‘other measures’ for details on these assessments. An accelerometer will be attached to measure physical activity for 7 subsequent days.

After the baseline assessment, participants will be randomised to one of the three study groups done by the nutritionists and they will inform the participants in which group they are allocated to. Participants randomised to one of the two intervention groups will be invited for a consultation meeting at the clinic to receive their personalise d dietary advice, and personalised advice on optimising the timing of protein intake in close proximity of usual physical activity (intervention group 2 only). This will take place within 2 weeks after the baseline assessment since the personalised advice needs to be composed by the nutritionist. The baseline assessment is considered the start of the study period for participants of the control group, while the consultation meeting is considered the start of the study period for participants of the intervention groups.

One week prior to the 3-month follow-up visit, dietary intake will be assessed again by means of a combination of three food diaries and three 24-hour dietary recalls. The 3-month follow-up visit will take place at the clinic and includes measurement of BW, assessment of self-reported mobility limitations, risk of sarcopenia, QoL, healthcare costs and the accelerometer will be attached to measure physical activity for 7 subsequent days.

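### Fixed blocks of three, with unblinded nutritionists assigning participants, make about one third of allocations certain in advance wherever staff know the earlier allocations in the block

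*Protocol article*

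**What the plan says.** The Randomisation, allocation and masking section of the Protocol article sets out the scheme:

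- Ratio: "Participants will be allocated in a 1:1:1 ratio to the three groups".
- Block size: "The size of the randomisation blocks is three". One size is given, with no variation.
- Strata: "Participants will be stratified according to their baseline habitual protein intake (<0.9 or 0.9–1.0 g/kg aBW/day) and sex". Site is mentioned in the same sentence, but not clearly as a stratification factor.
- Masking: "researchers, nutritionists and participants are not blinded to the study group".
- Who randomises: "Randomisation by means of a stratified block randomisation procedure will be performed by an independent statistician".

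The Study timeline section places randomisation after the baseline assessment and says "participants will be randomised to one of the three study groups done by the nutritionists and they will inform the participants" of their group.

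Three other sections show how much else the nutritionists do. Under Recruitment and screening, they conduct the dietary recalls that decide eligibility and the protein stratum. The Strengths and limitations box says they collect the data on all outcome measures. That box declares the lack of blinding as a limitation but does not mention that allocations may be predictable.

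**The concern.** Three is the smallest possible block for three arms at 1:1:1, and it is the easiest to work out. In an open trial, staff see each allocation as it is made. They do not need to see the list: the remaining place in a block follows from the places already used. Keeping the list hidden therefore does not by itself protect against this.

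The people who could make the deduction also meet candidates before randomisation. If a nutritionist knows or can guess the next arm, then enrolment can be encouraged, discouraged or re-timed, knowingly or not. The baseline 400 m walk can also be conducted with an expectation about the coming group. That walk is an eligibility test and also the baseline value of an effort-dependent primary outcome. Adjusting for baseline walk time does not fully repair a baseline measured under such an expectation, nor selection on unmeasured motivation.

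**Working it through.** **Inputs.** Block size 3, ratio 1:1:1, unblinded staff (Randomisation, allocation and masking). Planned total 264, with 132 per site and 44 per group per site (Sample size). Two stratifiers with two levels each give 2 × 2 = 4 strata, or 8 if lists are also kept per site.

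**The plan's own figure.** The article gives no predictability figure. Its sample size, used here only for the total, reproduces: a difference of 28 s with SD 61 s at two-sided 0.05 needs 75 per group for 80% power (power 0.803). Then 3 × 75 = 225, and 225 / 0.85 = 264.7, against the stated 264.

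**Exact arm.** With the earlier allocations in the block known:

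| Place in block | Arms still possible | Best-guess accuracy |
|---|---|---|
| 1 | 3 | 1/3 |
| 2 | 2 | 1/2 |
| 3 | 1 | 1 |

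- Share certain: 1/3 = 33.3%. If every block is complete, 264 / 3 = 88 allocations.
- Average best-guess accuracy: (1/3 + 1/2 + 1) / 3 = 61.1%, against 33.3% by chance.

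**Intervention versus control**, the contrast in the Statistical analyses plan. Place 3 is always certain. Place 2 is certain when control was drawn first (probability 1/3), because both remaining places are then intervention. Share certain: (0 + 1/3 + 1) / 3 = 44.4%.

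**Incomplete last blocks.** A stratum's last block leaves on average about one participant outside a complete block.

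- With 4 strata: (264 − 4) / 3 ≈ 86.7 certain allocations (32.8%).
- With 8 strata: (264 − 8) / 3 ≈ 85.3 (32.3%).

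Simulation of 264 participants gave the same averages. The exact-arm figure is therefore about one third, or roughly 85 to 88 of 264.

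**What staff must know.** These figures need knowledge of the earlier allocations in the block. With site-specific lists, the local nutritionists have it, because they made those allocations. If instead blocks span both sites, recruitment is evenly mixed and nothing is shared, a third-place participant's two predecessors both come from the same site with probability 1/2 × 1/2 = 1/4. The share with a fully known history is then 1/3 × 1/4 = 8.3%.

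**Comparison with larger blocks**, size fixed and known to staff:

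| Block size | Exact arm certain | Intervention vs control certain | Best guess, exact arm |
|---|---|---|---|
| 3 | 33.3% | 44.4% | 61.1% |
| 6 | 20.0% | 28.9% | 56.1% |
| 9 | 14.3% | 21.4% | 53.2% |

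Sizes 3 and 6 are by exact enumeration, size 9 by simulation. Varying the size without disclosing it lowers the certain shares further, since staff no longer know where a block ends. That gain was not computed.

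**The case against.** **Site is not clearly a stratifier.** Only protein intake and sex are named, so lists might run across both sites, and the 8% figure would then be nearer the truth. This stands as a condition on the result. Against it, the target of 44 per group per site suggests site-specific lists. The Intervention fidelity section also describes monthly meetings of staff from both sites, although it does not describe sharing allocations.

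**Safeguards exist.** Randomisation follows the baseline assessment, encouragement during the walk is standardised, the model adjusts for baseline walk time, and the analysing statistician is blinded. The first three reduce the risk. None prevents staff from deducing the next allocation before a candidate is enrolled or tested. Blinding the statistician does not bear on enrolment.

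**Predictability is not bias.** This stands. Unblinded outcome assessment is also a separate weakness, already declared, which would remain under any block size.

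A reader might also draw four stronger conclusions that the article does not support:

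- *At least one third of exact-arm allocations are predictable.* Incomplete blocks put the figure slightly below one third, and it is conditional on what staff know.
- *Staff decide whether a recall day counts as representative.* Recruitment and screening says the participant is asked. The other eligibility checks there are largely numeric, and re-contact is assigned to research staff, so the nutritionists' part in final enrolment is partly inferred.
- *The couples rule adds further forced allocations.* The second partner's arm is certain, but "Any resulting unbalance in the number of subjects per treatment arm will be corrected in the randomisation of the next block" also changes the composition of that block. The net effect cannot be computed from the text.
- *The article contradicts itself on who randomises.* "Randomisation by means of a stratified block randomisation procedure will be performed by an independent statistician" and "participants will be randomised to one of the three study groups done by the nutritionists" can both be true if the statistician generates the list and the nutritionists assign from it. This is a matter for clarification, and either reading leaves the predictability in place.

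**Conclusion.** The point holds in conditional form. A single fixed block size of three, with unblinded nutritionists assigning participants they have also screened, makes allocation largely guessable. If the earlier allocations in a stratum are known to staff, which is likely if lists are per site, then about one third of allocations (85 to 88 of 264) are certain for the exact arm, about 44% are certain for intervention versus control, and best-guess accuracy is 61% against 33%. If blocks span sites and no information crosses, the share with a fully known history falls to about 8%.

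This creates an opening for selective or re-timed enrolment and for expectation effects at the baseline walk. A reader might infer that the 400 m result is biased, but the article gives no basis for deriving the size, direction or presence of such a bias. The point is a design weakness with a cheap remedy. It does not show that the trial's comparison is invalid.

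**What to change.** **For participants still to be randomised:**

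- Replace the fixed block with undisclosed, randomly varying sizes, for example 3, 6 and 9, within strata, and state whether site is a stratum.
- Release each allocation only after eligibility and baseline data are locked. The article already orders these steps; a lock makes the order binding.

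The cost is a new list and a short amendment. Arms may end slightly unequal: an incomplete last block of 9 can leave two arms differing by at most 9 / 3 = 3 participants in that stratum.

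**In the text:** reconcile Randomisation, allocation and masking with Study timeline by saying that the statistician generates and holds the sequence and the nutritionists only assign from it, if that is what is meant.

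**If recruitment is closed:** the abstract's ethics statement puts consent in the past tense, and recruitment status is not shown, so a new list may no longer be possible. In that case, state the predictability as a limitation beside the lack of blinding, and compare baseline walk time by position in block, looking at the arms within the third place. With about 88 third-place participants, or 88 / 3 ≈ 29 per arm, this check is coarse, and finding no difference would not rule out selection. It needs only the stored allocation sequence and existing data.
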